### Intervention

Study therapists with a master’s degree in clinical psychology deliver the intervention within 48 hours of admission, as a single session of 45 minutes with the therapist by the bedside. Therapists are trained and supervised by senior clinical psychotherapists with degrees in psychology or psychiatry from the Clinical Psychology and Psychotherapy, Department of Psychology, University of Bern and Department of Psychiatry and Psychotherapy, University Hospital Zurich, Switzerland. Study therapists undergo at least 30 hours of training prior to beginning the trial. Two independent experts will rate 30 audiotaped intervention sequences to monitor adherence of study therapists to the intervention protocol. In addition, 50 patients from each intervention group will be asked to indicate their perception as to whether they belong to the intervention group A (that is, the *verum* group) or B (that is, the control group).

Table 1 details the components and topics of the two interventions. Each intervention consists of a counseling session of 45 minutes plus delivery of a colored information booklet for patients to deepen the oral information. Text and figures of the two booklets are specific to each mode of intervention and also serve as the basis for interacting with the patient. For the first half of the session, therapists will primarily cover topics that are of most immediate concern to the individual patient. For instance, when asking about previous stressful situations (in the control intervention) and the patient mentions a difficult situation at work, the discussion will be on job stress. Other forms of stressful life circumstances will not be covered but are dealt with in the information booklet. Nevertheless, during the course of counseling, therapists are required to inform about key topics, for instance, in the *verum* intervention, that it is a normal and common experience to perceive MI as stressful.

**Table 1 T1:** Topics and questions covered by the two interventions

***Verum *****group**	**Control group**
a) What is a trauma? Why can acute MI be understood as a traumatic experience?	a) What is psychosocial stress and when can it become dangerous?
b) Why can MI have a psychological impact?	b) Why do not all people react the same way to psychosocial stress?
c) How do patients cope with and adjust to their MI experience?	c) Which types of psychosocial stress are known to potentially have an influence on CHD and cardiac prognosis?

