d) What are the most common reactions to traumatically experienced MI?	d) How can psychosocial stress affect a healthy life style, adherence to cardiac therapy, and cardiovascular biology?
e) Other reactions to traumatically experienced MI.	e) What can be done to reduce psychosocial stress?
f) What is PTSD, in general and related to MI?	
g) Why do not all patients react in the same way to MI?	
h) Coping with the trauma, tackling avoidance, coping with safety behaviors, anxiety, anger/irritability, sleeping problems, alcohol and medication	
i) How to get professional help	

CHD, coronary heart disease; MI, myocardial infarction; PTSD, posttraumatic stress disorder.

The 45-minute *verum* intervention uses an educational and resource-oriented approach targeting individual patient resources and cognitive (re)structuring to specifically prevent MI-triggered traumatic reactions. The study therapist will introduce the concept of psychological trauma and PTSD and how MI patients may deal and cope with posttraumatic stress symptoms should these occur after MI [36,37,41,42]. The focus of the 45-minute control intervention is to inform patients about the role of psychosocial stress in CHD in general and how this information might be considered in re-building a life after MI for the sake of proper mental functioning [43-47]. Most importantly, the control intervention will completely avoid any terminology specifically pertaining to 'trauma’, including the MI as a trauma.

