Illness Perception Questionnaire-Revised (IPQ-R) [56,57]	x		
Beck Depression Inventory (BDI) [58-60]		x	x
Type D Scale (DS14) [61,62]		x	
Toronto Alexithymia Scale (TAS-20) [63,64]		x	
Resilience Scale [65,66]	x	x	
EuroQol group five dimension questionnaire (EQ-5D) [67,68]	x	x	x
Symptom Checklist-9 (SCL-9-K) [69,70]	x	x	x
Enhancing Recovery in Coronary Heart Disease Social Support Inventory (ESSI) [71,72]	x	x	
Global Mood Scale (GMS) [73]		x	x
Coping Inventory for Stressful Situations (CISS) [74,75]		x	
Heart drawing [76,77]	x		
Laboratory Analysis			
Metabolic factors: total cholesterol, LDL-C, HDL-C, triglycerides, glucose, HbA1c Routine laboratory measures: alanine transaminase, creatinine, hemoglobin, hematocrit, leukocytes, thrombocytes	x	x	x
Inflammation markers: hs-CRP, IL-6, TNF-α, IL-4	x	x	x
Hemostasis markers: fibrinogen, D-dimer, VWF antigen	x	x	x
Stress hormones: plasma cortisol, norepinephrine, epinephrine	x	x	x
Heart rate variability: total power, high frequency power, low frequency power, low-to-high frequency power ratio	x	x	x
Resting hemodynamics: heart rate, systolic/diastolic blood pressure	x	x	x
Anthropometric measurements: body weight, height, body mass index; waist and hip circumferences, waist-to-hip ratio	x	x	x
Developments since discharge from CCU/three-month assessment			
Vitality status		x	x
Hospital referrals since discharge (including recurrent cardiovascular events)		x	x
General practioner visits		x	x
Specialist visits		x	x
Cardiac rehabilitation		x	x
Psychotherapy since discharge		x	x
Recurrent cardiac symptoms		x	x
Medication adherence		x	x
Functional status		x	x
Treatment adherence with information booklet		x	x
Major life events		x	x
Onset of new diagnosis		x	x
Current medication		x	x

CCU, coronary care unit; HbA1c, hemoglobin A1c; HDL-C, high-density lipoprotein-cholesterol; hs-CRP, high-sensitive C-reactive protein; IL-6, interleukin-6; IL-4, interleukin-4; LDL-C, low-density lipoprotein-cholesterol; TNF, tumor necrosis factor; VWF, von Willebrand factor.

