### Ethical considerations

The study complies with the declaration of Helsinki. The ethics committee of the State of Bern, Switzerland, approved the study protocol. All potentially eligible patients (that is, those meeting the inclusion criteria) receive written information about the aim of the study, benefits and risks of participation and the exact study procedure before giving their written informed consent to participate in the study that includes two follow-up assessments. All participants are informed that they can withdraw themselves from the study anytime. All patients are encouraged to first contact their primary care physician in case they feel a need for mental health treatment at any time during follow-up. However, these patients will remain in the study, as it would be highly unethical to ask them to refrain from seeking professional help during follow-up. Patients who are diagnosed with syndromal PTSD at follow-up investigations are told their diagnosis. Moreover, patients and their primary care physicians are informed about the possibility of a referral to the Department of Clinical Psychology and Psychotherapy, University of Bern, Switzerland to receive treatment for PTSD.

To identify adverse reactions to the *verum* intervention, two interim safety analyses will be performed after subgroups of 130 and 260 patients on the primary efficacy endpoint, that is, interviewer-rated posttraumatic stress level at three months after the intervention. The spending function approximating O’Brien-Fleming boundaries [79] will be used to determine criteria for the interim and final analyses to protect the overall false positive rate of the trial at *P* = 0.05. The study will be stopped for inequality in outcome between the *verum* and control group if results reach a predefined level of statistical significance at the two-sided alpha level of 0.001 and 0.014, respectively. The nominal two-sided significance level for the final evaluation will be 0.045. This provides us with a 3.3% and 44.2% chance of stopping the trial after the first or second interim analysis, respectively.

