### Statistical analyses

Data will be analyzed using the latest version of the Statistical Package for the Social Sciences (SPSS Inc. Chicago, IL, USA) with a significance level of *P* < 0.05 (two-tailed). Before analysis, all outcome variables will be tested for normality by the Kolmogorov-Smirnov test and, if necessary, transformed to obtain a normal distribution. Differences in variables between the two intervention groups will be calculated using the *t*-test for continuous data and the chi-squared test for categorical data. The primary outcome is the severity of posttraumatic stress levels rated by the CAPS interview at the three-month follow-up. Secondary outcomes are measures of psychosocial functioning and cardiometabolic biomarkers at three months follow-up (primary analysis). Key secondary outcomes are quality of life, plasma levels of C-reactive protein, D-dimer, cortisol and norepinephrine, as well as high-frequency heart rate variability. These outcomes are important indicators of mental health functioning, low-grade inflammation and coagulation activity as well as hypothalamic-pituitary adrenal axis and autonomic nervous system function. Repeated measures analysis of variance will be applied to test for a change in posttraumatic stress levels and in measures of psychosocial functioning and cardiometabolic biomarkers between the two follow-up visits (secondary analysis). The relative risk for developing a diagnosis of PTSD during follow-up in the control group compared to the *verum* group will be calculated by means of logistic regression analysis. For a complementary sensitivity analysis, we will apply univariate, multivariate and repeated measures analysis of covariance taking into account sociodemographic, medical and psychosocial covariates, and received psychotherapy during follow-up.

Missing values for questionnaire items will be replaced using the expectation maximization algorithm [80]. If patients drop out during follow-up, we will carry forward the last observed data points to impute missing endpoints. Randomized patients who will not undergo the intervention are excluded from the analysis. However, we will perform an additional analysis based on the intention-to-treat principle with all randomized patients.

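### The sensitivity ANCOVA adjusts for psychotherapy received after randomisation, so it does not estimate the total effect of the session and cannot serve as a robustness check on the t-test

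*Protocol article*

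**What the plan says.** All references are to the protocol article.

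- **Main comparison (Statistical analyses).** It is unadjusted: "Differences in variables between the two intervention groups will be calculated using the *t*-test for continuous data", with a chi-squared test for categorical data. The abstract also names the t-test for the primary outcome.
- **Adjusted analysis (same section).** It is a supporting analysis by univariate, multivariate and repeated-measures ANCOVA, and its covariates are given only in general terms: "taking into account sociodemographic, medical and psychosocial covariates, and received psychotherapy during follow-up". No individual scale or time point is named for the sociodemographic, medical and psychosocial covariates. Psychotherapy is the one covariate whose timing is fixed by its own description.
- **Session timing (Intervention).** Therapists "deliver the intervention within 48 hours of admission, as a single session of 45 minutes".
- **Psychotherapy timing (Measures, Table 2).** The row "Psychotherapy since discharge" is marked at T1 and T2 only.
- **Session content (Intervention, Table 1).** The verum column includes "i) How to get professional help". The control column ends at item e) and has no such topic.
- **Help-seeking (Ethical considerations).** Patients in both arms who want mental health care are pointed to their primary care physician and stay in the study. In addition, "Patients who are diagnosed with syndromal PTSD at follow-up investigations are told their diagnosis", and they and their physicians learn of a possible referral for PTSD treatment.

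**The concern.** A covariate in a randomised comparison is safe when the intervention cannot have changed it. Psychotherapy during follow-up does not meet that condition, and the article supplies the reasons.

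If the session changes who seeks therapy, and symptoms also drive who seeks it, then comparing arms at equal therapy status compares patients who are no longer exchangeable. If therapy also lowers symptoms, adjustment removes part of what the session achieved.

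At stake is the supporting analysis. Agreement with the t-test would give false reassurance. Disagreement could not be read as fragility of the main result, because the two analyses answer different questions.

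**Working it through.** **1. The plan's own figure.** The point disputes no number, but the sample size shows what is and is not affected. With alpha 0.05 two-sided, power 80%, difference 2.9 and SD 10.1:

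n per group = 2 x (1.960 + 0.842)^2 x 10.1^2 / 2.9^2 = 2 x 7.849 x 102.01 / 8.41 = 190.4, so 191, or 192 with the t distribution.

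The plan states 194, which is reproduced closely. The calculation uses the unadjusted comparison, so the ANCOVA covariates do not enter it.

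**2. Order of events.** Randomisation, then the session within 48 hours of admission, then discharge, then psychotherapy since discharge (recorded at T1 and T2). The covariate is therefore post-randomisation by construction.

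**3. Paths in the document.**
- Arm to uptake: a topic on getting professional help appears in the verum column only.
- Symptoms to uptake: patients may seek care when they feel they need it.
- T1 outcome to later uptake: the diagnosis is disclosed and referral is offered. This acts after the T1 interview, so it concerns the 12-month and repeated-measures models and not the 3-month comparison.

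**4. Why the sign is open.** For least squares with arm and uptake as regressors, this identity is exact:

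unadjusted difference = adjusted difference + g x (p_V - p_C)

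Here g is the coefficient of uptake in the adjusted model, and p_V and p_C are uptake in the verum and control arms. Hence adjusted minus unadjusted = -g x (p_V - p_C). The sign of g depends on whether sicker patients seek therapy (positive) or therapy lowers scores (negative). The sign of p_V - p_C depends on whether the session promotes help-seeking (positive) or lowers need (negative). The document fixes neither.

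**5. Illustration.** Every uptake and therapy figure below is an assumption. The scale is PDS points from the sample size section, whereas the primary outcome is CAPS. Two million patients were simulated per row:
- Symptoms = 14.2 + 10.1 x (0.8u + 0.6e) - effect x arm, with u and e standard normal.
- Log-odds of uptake = log(0.15/0.85) + log(OR arm) x arm + log(OR per SD) x (symptoms - 14.2)/10.1.
- Outcome = symptoms - benefit x uptake + noise with SD 3.

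| True effect on symptoms | OR arm | OR per SD | Therapy benefit | Uptake verum / control | Unadjusted | Adjusted | Shift |
|---|---|---|---|---|---|---|---|
| -2.9 | 1 | 1 | 0 | 15.0% / 15.0% | -2.89 | -2.89 | 0 |
| -2.9 | 1 | 2.72 | 0 | 15.3% / 18.8% | -2.91 | -2.60 | +0.31 |
| -2.9 | 2.01 | 2.72 | 0 | 24.9% / 18.8% | -2.88 | -3.41 | -0.53 |
| -2.9 | 2.01 | 1 | 3 | 26.3% / 15.0% | -3.22 | -2.89 | +0.33 |
| 0 | 2.01 | 2.72 | 0 | 29.7% / 18.9% | +0.03 | -0.91 | -0.94 |

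Checking the third row against the identity: g = 0.53 / (0.249 - 0.188) = 8.7 points, meaning therapy users are much sicker. The fourth row shows the mediator case: adjustment removes 3 x (0.263 - 0.150) = 0.34 points of genuine effect, up to simulation error.

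A second model let uptake follow underlying severity that the session does not change, with no therapy benefit and log-odds of 0.7 to 1.5 per SD. For a true -2.9, the adjusted estimate ran from -2.9 (15% in both arms) to about -4.3 (10% control, 25% verum). With 3% against 5% it was only about -3.0 to -3.1. With uptake driven by symptoms alone, reruns gave values as weak as about -2.3.

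**The case against.** **Only a supporting analysis is involved.** This stands. The t-test, the sample size and the interim boundaries do not use the ANCOVA, and the article does not require the two to agree. A reader might infer that the primary result is compromised; nothing in the document supports that.

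**Dependence on arm is thinly evidenced.** Getting help is one of nine verum topics, and patients in both arms are pointed to their physician. This is fair as to size: at three months the bias could be negligible. It does not make the covariate a baseline one, and uptake that depends on symptoms alone already shifts the estimate whenever the session works.

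**The investigators may want the effect net of outside therapy.** That is a legitimate question, but a different one. It needs the assumption that no unmeasured factor drives both therapy and symptoms, and it is not a sensitivity analysis of the t-test.

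**Two stronger readings are tempting.** One is that adjustment overstates the benefit. Section 4 and the table show it can go either way. The other is that the psychosocial covariates share the defect, because BDI, DS14, TAS-20, GMS and CISS have no T0 value in Table 2. The article does not say that any of these will be a covariate. PDS, ASDS, IPQ-R, Resilience Scale, EQ-5D, SCL-9-K and ESSI all have T0 values, so the sentence can be carried out with baseline scales. A condensed article may also leave the covariate list to the full plan.

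**Conclusion.** The point holds for the psychotherapy covariate. The article expressly names a post-randomisation variable as a covariate and itself indicates that it can depend on arm and symptoms and, for the later models, on the 3-month outcome. Followed as written, the adjusted model does not estimate the total effect of the session and cannot confirm or undermine the t-test.

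No size or sign can be given from the document. The figures above rest on assumed uptake and show only that shifts of a few tenths of a point up to more than one point, in either direction, are possible, as is no shift at all. There is no bias if uptake depends on neither arm nor symptoms. The consequence is a misread supporting analysis, with the confirmatory result intact, so this is a change that should be made rather than one on which the trial depends.

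**What to change.** In Statistical analyses, remove psychotherapy received during follow-up from the sensitivity ANCOVA, and state that all its covariates, including any psychosocial ones, are limited to values measured at T0 before the session. No particular covariate list is needed.

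Report psychotherapy uptake by arm at T1 and T2 descriptively. If a psychotherapy-adjusted model is still wanted, label it an exploratory mediation analysis, state its assumptions, and do not present it as a check on the primary result.

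The cost is a sentence or two in the plan. Uptake is already collected at both visits, so no data, sample size or primary analysis changes.

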The primary aim of our randomized-controlled trial is to examine whether the development of posttraumatic stress can be reduced by a single counseling session of 45 minutes targeting MI-triggered traumatic reactions (that is, the *verum* intervention). The effect of this counseling session will be tested against a control intervention targeting the general role of psychosocial stress in CHD. The verum and control interventions are both administered to patients at high risk to develop PTSD within a setting of a coronary care unit (CCU) within 48 hours by the bedside after patients having reached stable circulatory conditions. Secondary aims of our trial are to investigate psychosocial functioning and cardiometabolic risk markers between the two active intervention arms.

Our main hypothesis is that trauma-focused psychological counseling is more effective than non-trauma focused counseling for reducing posttraumatic stress after acute MI. Specifically, we predict that compared with the control group, the verum group will report at least 20% lower posttraumatic stress levels at three months after MI as rated by blinded interviewers (primary outcome). We expect that this group difference will persist for up to 12 months. Compared to the control group, the verum group will additionally show better psychosocial functioning and a more favorable profile of cardiometabolic risk markers after 3 and 12 months of follow-up (secondary outcomes).

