### Measures

Table 2 shows all health outcomes in the MI-SPRINT study with the timing of their assessment. All psychometric questionnaires used in the MI-SPRINT study are validated in the German language [48-77]. We will apply the Clinician-Administered PTSD Scale (CAPS) to assess our primary outcome (that is, interviewer-rated posttraumatic stress level at three months after the intervention) [48]. Assessors will be blinded to the type of intervention and asked to indicate their guess as to whether the patient had received the *verum* intervention or the control intervention. The German version of the CAPS shows good internal consistency for the severity score of all 17 PTSD symptom items (Cronbach’s α = 0*.*88 to 0.92) as defined by the *DSMcpIV*[49]. The frequency and intensity of each symptom are rated between 0 (never) and 4 (almost always). A symptom is given when frequency is at least one point and intensity is at least two points. One of five symptoms is required for criterion B (reexperiencing cluster), three of seven symptoms for criterion C (avoidance cluster), and two of five symptoms for criterion D (hyperarousal cluster). The severity of PTSD is obtained by adding up symptom scores of criteria B+C+D. Patients will be diagnosed with syndromal PTSD if meeting criteria B+C+D [1].

**Table 2 T2:** Measures at hospital referral (T0), three-month (T1) and twelve-month (T2) follow-up

**Variables**	**T0**	**T1**	**T2**
Sociodemographic and medical variables			
Demographics: for example, gender age, marital status	x		
Medical history: for example, family history of coronary artery disease, diabetes mellitus, hypertension	x		
Lifestyle and health behavior: smoking history, alcohol consumption, physical exercise, sleep quality	x	x	x
Prescribed medication before CCU referral	x		
Medication administered during CCU stay	x		
Medication at discharge from CCU	x		
Context of hospital referral: for example, patient agitation state at arrival on CCU, hectic conditions on CCU at patient arrival	x		
Clinical presentation at time of arrival at CCU: for example, total number of stents implanted, number of diseased coronary vessels, left ventricular function, Killip classification, pain onset	x		
Psychometric data			
Clinician-administered PTSD Scale (CAPS) [48,49]		x	x
Posttraumatic Diagnostic Scale (PDS) [50,51]	x	x	x
PTSD screening with three items from the structured clinical interview for DSM-PTSD [52,53]	x		
Acute Stress Disorder Scale (ASDS) [54,55]	x		

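### The carry-forward rule for drop-outs cannot fill a missing three-month CAPS (the primary endpoint), because CAPS is not measured at T0; where the rule can run, it enters acute-phase values as follow-up results

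*Protocol article*

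**What the plan says.** Under Statistical analyses, the primary endpoint is defined thus: "The primary outcome is the severity of posttraumatic stress levels rated by the CAPS interview at the three-month follow-up". The same section gives two missing-data rules. Single questionnaire items are filled by expectation maximization. For patients who leave the study, the rule is "If patients drop out during follow-up, we will carry forward the last observed data points to impute missing endpoints". No outcome is exempted.

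Randomized patients who do not undergo the intervention are left out of the main analysis, and the section then adds: "However, we will perform an additional analysis based on the intention-to-treat principle with all randomized patients".

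Table 2 in the Measures section, titled "Measures at hospital referral (T0), three-month (T1) and twelve-month (T2) follow-up", marks the row "Clinician-administered PTSD Scale (CAPS) [48,49" at T1 and T2 and leaves T0 blank. PDS is marked at all three visits. The Background states the 12-month hypothesis: "We expect that this group difference will persist for up to 12 months". The Sample size calculation section expects drop-outs, post-MI mortality among them, and raises 194 per group to 213.

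**The concern.** Carrying forward needs an earlier value of the same measure. The primary endpoint is read at the first visit at which CAPS is taken, so there is none. The plan then has no working rule for a missing primary endpoint. The primary comparison falls back on patients with an observed CAPS, or on a method chosen after the data are seen.

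Outcomes that do have a T0 value raise a second problem. T0 lies in the coronary care unit, hours after the infarction. C-reactive protein, D-dimer, cortisol, norepinephrine and high-frequency heart rate variability are key secondary outcomes, as is quality of life (EQ-5D in Table 2). All have a T0 value that the rule would enter as the three-month result.

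A third problem arises at T2. A copied T1 value sets a patient's change to zero, and change between the two follow-up visits is what the repeated-measures analysis of variance tests.

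**Working it through.** **1. Can the rule run at T1?** From Table 2:

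| Outcome | T0 value | Effect of the rule for a patient lost before T1 |
|---|---|---|
| CAPS (primary) | none | nothing to carry |
| BDI, GMS, DS14, TAS-20, CISS | none | nothing to carry |
| PDS, EQ-5D, SCL-9-K | yes, within 48 hours of MI | acute value entered as three-month value |
| CRP, D-dimer, cortisol, norepinephrine | yes, blood drawn within 24 hours of referral | acute value entered as three-month value |
| Heart rate variability | yes | acute value entered as three-month value |

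No other text closes the gap for CAPS. Expectation maximization is stated for questionnaire items, not for an interview that never took place. PDS exists at T0, but it is a separate self-rated scale and nothing substitutes it for CAPS.

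**2. The plan's own sample size.** Inputs from Sample size calculation: difference 2.9, SD 10.1 (both PDS), alpha 0.05 two-sided, power 80%.

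n = 2 × (1.96 + 0.842)² × 10.1² / 2.9² = 190.4, so 191 per group; the t-based solution is 191.4, so 192. The stated 194 is reproduced within 3%.

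**3. How many patients are involved?** The allowance is 213 − 194 = 19 per group, so 2 × 19 = 38 of 426 (8.9%). It covers drop-out in general; the share lost before T1 is not given.

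**4. What carrying T0 forward does where it can run.** Assumptions not in the document: a share m of each arm is missing at T1, the arms have equal T0 means, the SD is the same at T0 and T1, and missingness is unrelated to outcome. The imputed share then contributes no difference, and the expected difference is (1 − m) × 2.9:

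- m = 5%: 0.95 × 2.9 = 2.75 (2.755)
- m = 10%: 0.90 × 2.9 = 2.61
- m = 20%: 0.80 × 2.9 = 2.32
- m = 30%: 0.70 × 2.9 = 2.03

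Power at m = 10%, alpha 0.05, 213 randomized per group:

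- Observed cases only: n = 213 × 0.9 = 191.7; SE = 10.1 × √(2/191.7) = 1.03; 2.9/1.03 − 1.96 ≈ 0.85; power 80.3%.
- T0 carried forward, no mean shift from T0 to T1: SE = 10.1 × √(2/213) = 0.98; 2.61/0.98 − 1.96 ≈ 0.71; power 76.0%.
- T0 carried forward, T0 mean 10 points above T1 (assumed): SD = √(10.1² + 0.1 × 0.9 × 10²) = 10.54; power 72.5%.

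If loss differs between arms, the direction can change. With no true effect, a 10-percentage-point gap in loss and an assumed T0–T1 shift of 5 to 10 points, the rule creates a difference of 0.10 × 5 = 0.5 to 0.10 × 10 = 1.0 point.

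**5. What copying T1 to T2 does.** Let d1 and d2 be the true differences at T1 and T2, and q the share copied in each arm, with missingness unrelated to outcome. The T2 difference becomes (1 − q) × d2 + q × d1, and the between-arm difference in change becomes (1 − q) × (d2 − d1). Both are pulled towards no change, that is, towards the hypothesised persistence. The document gives no CAPS difference, CAPS SD or drop-out share at T2, so this cannot be put in CAPS points.

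**The case against.** The strongest reply is that harm to the primary test is not shown. The trial is sized so that about 194 per group remain after drop-out, and 10% loss with analysis of observed cases still gives 80.3% power on the PDS inputs. No bias in the CAPS contrast can be calculated from the document. This stands, and it limits the claim on size. It does not make the rule workable.

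A reader might also infer more than the text supports:

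- *That about 43 patients (10% of 426) will lack a T1 CAPS.* The allowance is 38, it is an allowance and not a forecast, and it is not tied to loss before T1.
- *That the intention-to-treat analysis cannot be run.* That sentence answers the exclusion of patients who did not undergo the intervention. They can be restored to their allocated arm wherever they have follow-up. The gap concerns only those without a T1 CAPS.
- *That standard errors will be too small.* Single imputation treats filled values as observed, but in the illustration a T0–T1 shift adds variance and lowers power. Underestimation is not demonstrated here.
- *That values will be imputed for patients who have died.* Mortality is mentioned only in sizing the trial, and vitality status is recorded at both follow-ups. The plan is silent on this.
- *That a T0 PDS would produce a PTSD diagnosis.* The diagnosis comes from CAPS criteria; a carried PDS stays a PDS score.

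It is also fair that a repeated-measures model alone gains no outcome information from patients missing both CAPS visits.

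**Conclusion.** The point holds. It rests on two statements that cannot both be carried out: a carry-forward rule with no exemption, and a visit schedule with no T0 CAPS. This needs no assumption, and it is not a detail left to an analysis plan, because the article fixes the rule. For T1 CAPS, and for BDI, GMS, DS14, TAS-20 and CISS at T1, the rule fills nothing. The additional analysis of all randomized patients has no workable rule for those without a T1 CAPS.

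For outcomes with a T0 value the rule runs but enters acute-phase values at T1. At T2 it imposes no change on copied patients. The size and direction of the resulting bias cannot be fixed from the document. The reduction from 2.9 to 2.61 points is an illustration on the PDS scale under an assumed 10% missing per arm and equal T0 means. It should not be read as the expected bias in CAPS.

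**What to change.** - Delete the carry-forward sentence. Do not carry T0 values to T1 or T1 values to T2, for any outcome.
- For T1 CAPS, use multiple imputation by arm from T0 ASDS, PDS and the distress ratings, plus any observed T1 or T2 PDS and T2 CAPS. Keep the planned between-group comparison, applied to the imputed data sets and pooled. Use the same imputation in the analysis of all randomized patients.
- A likelihood-based repeated-measures model is an option for T2 and for patients with at least one follow-up value.
- Add a delta-adjusted sensitivity analysis that makes the imputed CAPS values progressively less favourable, to show how far the conclusion depends on the missing-data assumption.
- State that values are not imputed after death, and report deaths by arm.

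The predictors are already scheduled, so no extra data or patients are needed. The cost is protocol and analysis-plan wording, modest programming, and an analysis slightly more complex than a t-test on filled data.
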